## Introduction

Heavy metals such as cadmium (Cd), mercury (Hg), and lead (Pb) exist in water, air, and food, contributing to cumulative exposure in humans [1,2]. According to the World Health Organization (WHO), Pb exposure alone is responsible for nearly 1 million deaths annually and more than 21 million disability-adjusted life years (DALYs) lost, with more than 95% of this burden occurring in low- and middle-income countries (LMICs) [3]. Prenatal exposure to Pb and other heavy metals is particularly harmful as it has been linked to miscarriage, preterm birth, low birth weight (LBW), and developmental problems in children [4-6]. Studies have shown that no level of lead exposure is considered safe during pregnancy, and even low-dose exposures can disrupt fetal development. These risks highlight the urgent need for public health interventions targeting environmental metal exposures in vulnerable populations, especially among pregnant women in LMICs where monitoring and remediation remain limited.

In Makassar, Indonesia, 717, 347, and 816 LBW cases were reported in 2021, 2022, and 2023, respectively. Preliminary investigation also revealed significantly elevated levels of blood Pb (1.35–101.00 μg/L) and Cd (0.55–17.00 μg/L), exceeding reference values in various countries [7]. For context, the US Centers for Disease Control and Prevention (CDC) considers blood Pb levels above 5 μg/dL (50 μg/L) as elevated in adults [8-10], while the WHO identifies Cd concentrations exceeding 1 μg/L in blood as potentially toxic. These findings highlight a concerning level of environmental exposure during pregnancy. Although specific to Makassar, such elevated exposures reflect broader environmental health challenges in urban Indonesia and Southeast Asia, where industrial emissions, traffic pollution, and inadequate regulation contribute to rising heavy metal contamination.

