### Data Analysis

All analyses will be conducted using the R statistical software (latest version). Data entry and cleaning will be conducted by trained staff using a double-entry verification. For 24-hour food recall data, participants will be asked to estimate portion sizes using visual aids, and data will be reviewed during collection for completeness and clarity. For the FFQ, if participants leave implausible answers (eg, extremely high frequency), the data will be reviewed and clarified during the interview or excluded from analysis after documentation. Implausible intake frequency will be cross-checked with interview notes and food recall summaries to determine plausibility. An intention-to-treat (ITT) analysis will be performed to preserve the benefits of initial group allocation. For missing or partial responses, multiple imputation will be considered for covariates in the adjusted models. For missing outcome data at follow-up, last observation carried forward (LOCF) will be used when feasible. Sensitivity analyses will be conducted to assess the robustness of findings under different missing data assumptions. Outliers will not be automatically excluded unless clear reporting errors are confirmed. Outliers in biomarker measurement will be identified using the interquartile range method and retained unless proven to result from analytic error or sample contamination. All statistical analyses will be conducted with and without outliers to assess the robustness of the results.

Descriptive statistics will summarize participant characteristics. All continuous variables, including heavy metal concentrations and biomarker levels, will be checked for normality before analysis. In the case of non-normal distributions, appropriate data transformations (eg, log transformation) will be applied. If normality cannot be achieved, nonparametric tests (eg, Mann–Whitney *U* or Wilcoxon signed-rank test) will be used as alternatives. Analysis of group differences (pre- and postintervention). For each group, analysis will be conducted using the paired *t* test or Wilcoxon signed-rank test, depending on data distribution, to assess changes in heavy metals, MDA, and 8-OHdG levels before and after intervention. The significance level (alpha) will be set at .05, and all tests will be one-tailed.

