For comparison between the groups (intervention vs control), analysis will be conducted using the difference-in-differences (DiD) method to measure the difference in changes between the intervention and control groups. The results will provide an overview of the impact of moringa leaf supplementation on the reduction of heavy metal levels and prevention of DNA damage in pregnant women. To address potential selection bias and confounding due to the nonrandomized design, we will use analysis of covariance (ANCOVA) to adjust for baseline differences in key variables such as maternal age, gestational age, education level, and baseline levels of heavy metals, MDA, and 8-OHdG.

Assumptions for ANCOVA will be checked using diagnostic plots and tests. Normality of residuals will be checked using the Shapiro–Wilk test and Q-Q plots. The homogeneity of variance test will use the Levene test from the car package. Linearity and homoscedasticity will be checked using residual versus fitted plots.

The interaction effects between intervention status and baseline heavy metal levels will be examined by adding interaction terms to the ANCOVA models. Additionally, stratification will be considered a sensitivity analysis to minimize bias. Baseline heavy metal levels will be included as covariates in the statistical models to account for variation in environmental exposure across recruitment areas. In addition, we will conduct exploratory subgroup analyses to assess potential effect modifiers. Outcomes will be examined separately for each heavy metal to assess whether the reduction effect of *M. oleifera* differs by metal type. Additional exploratory subgroup analyses may include stratification by trimester of pregnancy, nutritional status (BMI), and geographic location/pollution source.

If substantial differences are observed, these findings will be interpreted cautiously due to limited statistical power. All subgroup analyses will be considered hypothesis generating and reported transparently. If no significant interaction is found, primary analyses will focus on aggregate outcomes across all participants. Reduction in each individual heavy metal will be reported separately, along with a composite index. No interim analyses or stopping rules are planned due to the short duration of the trial and the nature of the design.

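### Separate per-metal analyses are given the task of showing whether moringa's effect differs between metals, but no stated analysis compares the metals with each other

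*Protocol article*

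**What the plan says.** All of this is in the protocol's Data Analysis section unless stated otherwise.

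- The between-metal question and its method come in one sentence: "Outcomes will be examined separately for each heavy metal to assess whether the reduction effect of *M. oleifera* differs by metal type".
- One interaction is defined: "The interaction effects between intervention status and baseline heavy metal levels will be examined by adding interaction terms to the ANCOVA models". This concerns how high a woman's metal level was at the start, not which metal is considered.
- A later sentence refers to an interaction without naming it: "If no significant interaction is found, primary analyses will focus on aggregate outcomes across all participants".
- On reporting: "Reduction in each individual heavy metal will be reported separately, along with a composite index".
- On error level and direction: "The significance level (alpha) will be set at .05, and all tests will be one-tailed".
- On status: "If substantial differences are observed, these findings will be interpreted cautiously due to limited statistical power", and "All subgroup analyses will be considered hypothesis generating and reported transparently".
- Log transformation is offered as a remedy where a variable is not normally distributed, with rank tests if that fails. It is not set as the common scale for the three metals.

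The Introduction gives blood lead in Makassar as 1.35 to 101.00 μg/L and cadmium as 0.55 to 17.00 μg/L. The Expected Outcomes section makes reduction in these metals the primary outcome, and says they will be reported individually and, if appropriate, in aggregate.

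**The concern.** The question has equal effects on lead, cadmium and mercury as its null hypothesis. Each separate analysis has no effect on one metal as its null hypothesis. Three answers to the second question do not add up to an answer to the first. One metal may cross the significance threshold while another narrowly misses it with almost the same estimate. Conversely, two metals may both be significant with quite different effects.

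The scale adds a second difficulty. The metals circulate at different concentrations, so equal proportional falls give unequal falls in μg/L. Because transformation depends on each variable's distribution, one metal could be analysed raw, another logged and a third by ranks. The estimates would then share no scale even for informal comparison.

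At stake is a statement that moringa acts on some metals more than others, made without an analysis that could support it. The same question bears on whether an aggregate of the three metals is a sensible summary.

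**Working it through.** **The plan's own figures.** The protocol gives no effect size, power or sample size for a comparison between metals, so there is no figure for this point to reproduce. Its one effect size is for 8-OHdG: 12.96 / 30.68 = 0.422, stated as 0.42, which reproduces. (The 37 per group derived from it does not reproduce as a two-group sample size: the one-sided formula gives 71. That is a separate matter.)

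**Inputs**
- From the protocol: one-sided α = .05; 26 per group (Results), 37 and 44 per group (sample-size paragraph), 59 per group (Participant Recruitment).
- Assumed: a true standardised effect d = 0.42 on the change in every metal, and correlation ρ between metals of 0 to 0.7. The protocol gives neither for any metal.

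**Step 1: power for one metal.** Power = Φ(d√(n/2) − 1.645).
- n = 26: 0.42 × 3.606 − 1.645 = −0.131, power 45%.
- n = 59: 0.42 × 5.431 − 1.645 = 0.636, power 74%.

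**Step 2: chance that the three tests disagree** (one or two of three significant) when all true effects are equal. For independent metals with power p, this is 1 − p³ − (1 − p)³ = 3p(1 − p).
- n = 26: 3 × 0.448 × 0.552 = 0.742.
- n = 59: 3 × 0.738 × 0.262 = 0.580.

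For correlated metals the values come from trivariate-normal simulation.

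| Per group | Power per metal | ρ = 0 | ρ = 0.2 | ρ = 0.3 | ρ = 0.5 | ρ = 0.7 |
|---|---|---|---|---|---|---|
| 26 | 45% | 74% | 65% | 60% | 50% | 38% |
| 37 | 56% | 74% | 64% | 60% | 49% | 38% |
| 44 | 63% | 70% | 61% | 57% | 47% | 36% |
| 59 | 74% | 58% | 51% | 48% | 40% | 31% |

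**Step 3: sensitivity to the assumed effect.** A different effect size acts through the per-metal power. The ranges below run from ρ = 0 to ρ = 0.7.
- Power 30% or 70%: 63% to 33%.
- Power 20% or 80%: 48% to 26%.
- Power 90%: 27% to 16%.
- No effect on any metal (each test significant 5% of the time): 3 × 0.05 × 0.95 = 14%, falling to 9%.

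Even with independent metals, disagreement exceeds one half only where 3p(1 − p) > 0.5, that is, for power between about 21% and 79%.

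**Step 4: a direct test.** A two-degree-of-freedom within-woman test of equal standardised effects, simulated under equal effects at 26, 37 and 59 per group with ρ of 0, 0.3 and 0.5, rejected in 4.6% to 5.6% of trials, close to its nominal 5%. Its power is low. The smallest difference between two metals detectable with 80% power (two-sided .05) is (1.960 + 0.842) × √(2/n) × √(2(1 − ρ)). At 26 per group this is 1.10 SD for ρ = 0 and 0.78 SD for ρ = 0.5; at 59 per group it is 0.73 and 0.52 SD.

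**Step 5: scale.** Under any common proportional fall, the absolute fall in lead relative to cadmium equals the ratio of their levels: 101.00 / 17.00 = 5.9 at the tops of the reported ranges, and 1.35 / 0.55 = 2.5 at the bottoms.

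**The case against.** The strongest reply is that the protocol never says a difference will be declared because one metal is significant and another is not. A reader might infer that rule from the sentence, but the text says only that the metals are examined separately. Estimates with intervals could be set side by side instead. This stands, and it makes the disagreement rates conditional on how the results are read. It does not supply a comparison: informal inspection is not a test of equality, and without a common scale it is also hard to do.

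The question is exploratory, and the protocol says so. This stands and limits the consequence. But caution about power addresses imprecision, not a method that answers a different question.

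The unnamed interaction in "If no significant interaction is found, primary analyses will focus on aggregate outcomes across all participants" could loosely be taken to include metal type. No such term is defined, though, and the one that is defined concerns baseline level. Nor is this merely detail left to an analysis plan that is not shown, because the article itself pairs the question with a method.

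The calculation is also a simplification. It uses change scores rather than baseline-adjusted ANCOVA, and the direct test in Step 4 compares standardised effects rather than the log ratios recommended below. It shows the order of size, not the trial's exact operating characteristics.

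**Conclusion.** The mismatch between question and method holds: the plan aims to assess differences between metals, and no stated analysis does so. If differences were read from the separate significance results, equal effects could often look different: about 38% to 74% of trials at 26 per group and 31% to 58% at 59 per group. This rests on d = 0.42 for every metal, borrowed from 8-OHdG, and on assumed correlations of 0 to 0.7.

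Three stronger readings go beyond the documents.
- That equal effects would usually look different. Several cells of the table fall below one half, and the figure is 14% or less if no metal responds.
- That the trial would report detoxification that is only chance. In the calculation all three effects are real; only the apparent difference between them is chance.
- That a false difference would decide the target of later studies. The Future Directions section proposes larger randomised trials, dose-response work, further biomarkers and birth outcomes, and selects no metal.

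This is a minor point about an exploratory question, worth correcting because the correction is cheap.

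**What to change.** Take one of two routes.

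1. **Keep the question and test it.** Replace the sentence with one joint model of the follow-up log concentrations of the three metals. Adjust each metal for its own baseline log value and the planned covariates, and allow for correlation within a woman (unstructured covariance or a woman-level random effect). Test the intervention-by-metal interaction two-sided, as an exception to the one-tailed rule, since a difference between metals has no predicted direction. Report the three intervention-to-control ratios, and the differences between them on the log scale, with confidence intervals. Use the log scale for all three metals whatever the normality checks show. Keep the separate per-metal estimates, but not as evidence that effects differ.

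2. **Drop the question.** Delete the aim of assessing differences by metal type, and label the per-metal results descriptive.

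The first route costs one extra model on data already being collected. Its limits should be stated. The test has low power (Step 4), so the likely answer is that no difference was shown, which is not evidence of equal effects. Because the six centres were not randomised and differ in pollution source, an interaction could also reflect local exposure rather than moringa, and would remain hypothesis generating. The second route costs only the wording.

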## Methods

### Study Design

This study is an ongoing quasi-experimental investigation that uses a nonrandomized pre-post test methodology. Expectant mothers were divided into 2 cohorts, one receiving an intervention and the other serving as a control. This study applied a nonrandomized pre-post test design due to practical considerations related to (1) practical management, (2) geographical differences, and (3) time constraints.

First, practical management considers that managing the study is easier when specific locations are designated for the intervention group and other locations for the control group. This approach ensures that the intervention (*M. oleifera* supplementation) can be efficiently delivered and monitored in each location without the complexity of randomizing participants across multiple sites. Furthermore, grouping participants by location helps streamline logistical operations such as monitoring compliance and ensuring consistent follow-up over the course of the intervention period.

Second, although the geographical settings of the intervention and control groups may differ, they were comparable in terms of demographic characteristics and environmental conditions. This allowed us to evaluate the effects of moringa supplementation in different geographical settings while maintaining comparability between groups. In addition, by focusing on distinct locations for intervention and control, we ensure better resource allocation and minimize the logistical challenges that would arise from attempting to randomize participants across a broader region.

Third, time was considered a constraint due to limitation in the laboratory. We could not receive heavy metal analysis results from the initial screening at the same time for all participants. Therefore, women with high levels of heavy metals at the first screening were included in the intervention group to avoid delays. This ensures that these participants can begin the 2-month intervention with *M. oleifera* as soon as possible after obtaining the result, considering the limited research timeframe. Furthermore, because we limited the overall time for the study, randomizing participants could cause delays in implementing the intervention and complicate the process of ensuring that those with high levels of heavy metals receive timely treatment.

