### Participant Recruitment

This research has been conducted in Makassar City, specifically at 6 community health centers where expectant women receive prenatal services. The 6 selected community health centers are located in areas with varying environmental characteristics, including industrial zones, regions near landfill sites, and coastal areas. While the types of pollution sources differ, all sites share a common feature: exposure to potential environmental contaminants. Each represents an urban setting with a plausible risk of heavy metal exposure through air, water, and food pathways. Thus, despite differences in specific pollution types, the study sites are considered comparable in terms of overall environmental risk exposure. This selection strategy ensures that the intervention and control groups are drawn from communities facing similar environmental health challenges. Moreover, such variation may enhance the generalizability of findings across different urban pollution contexts. Three centers were assigned as intervention sites and 3 as control sites based on operational convenience and to avoid information spillover between groups.

The study will include 59 pregnant women in each group of intervention and control who underwent an examination at health centers in Makassar and fulfilled the following inclusion criteria: (1) pregnancy during the second or third trimester, (2) intention to deliver in Makassar, (3) living in Makassar for a period exceeding 1 year, and (4) blood levels of Hg, Pb, or Cd exceeding the reference value. Participants will be excluded based on self-report during interview if they (1) are having twin pregnancy, (2) had known chronic medical conditions, such as diabetes, cancer, kidney diseases, (3) are taking other antioxidant or mineral supplements beyond standard care, (4) are diagnosed with micronutrient deficiencies, (5) relocate during the intervention period, and (6) are unwilling to comply with follow-up procedures.

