The required sample size was calculated using an estimated effect size (Cohen *d*) of 0.42, derived from a previous intervention study in South Sulawesi, which assessed the effects of *M. oleifera* supplementation on oxidative stress biomarkers in pregnant women exposed to passive smoking [37]. The study reported a mean difference in 8-OHdG levels between treatment groups of approximately 12.96 ng/mL with a pooled SD of ~30.68 ng/mL, yielding a moderate effect size. Using a 1-sided test with *α*=.05 and 80% power, the minimum required sample size is 37 participants per group. To account for an anticipated 20% dropout rate, the sample size was increased to 44 participants per group, yielding a total of 88 participants.

Approximately 200 pregnant women attending routine antenatal care (ANC) visits at the community health centers were sequentially approached and invited to participate in the study. They were first interviewed to determine eligibility based on inclusion and exclusion criteria. Those meeting the criteria were provided with detailed information about the study and asked to provide written informed consent. Following consent, a blood sample was collected to assess baseline levels of heavy metals.

Only participants with elevated levels above reference thresholds were considered eligible for inclusion in the intervention phase. For the intervention group, eligible participants were contacted and provided with *M. oleifera* supplements along with instructions for daily consumption over a 2-month period. They were informed that a follow-up blood collection would occur at the end of the supplementation period during a routine visit.

For comparison, the control group was recruited from a different health center in a separate subdistrict administrative unit that did not receive moringa supplementation. This approach minimized contamination between groups and allowed for feasible implementation of the intervention. Follow-up blood sampling was also conducted after 2 months, aligned with their next scheduled antenatal visit, but without providing moringa supplementation.

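### Stratifying by geographic location cannot show where moringa works, because each centre belongs to one arm; by pollution source it can do so only for types present in both arms

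*Protocol article*

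**What the plan says.** Under Data Analysis, the article plans exploratory subgroup analyses to look for effect modifiers and adds: "Additional exploratory subgroup analyses may include stratification by trimester of pregnancy, nutritional status (BMI), and geographic location/pollution source". Subgroup results are to be treated as hypothesis generating and read cautiously because power is limited. The contrast between the arms is a difference-in-differences, with ANCOVA to adjust for baseline differences.

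The arms are defined by place. Study Design explains that "managing the study is easier when specific locations are designated for the intervention group and other locations for the control group". Participant Recruitment says the study runs "specifically at 6 community health centers where expectant women receive prenatal services" and that "Three centers were assigned as intervention sites and 3 as control sites based on operational convenience and to avoid information spillover between groups". It describes the settings of the six centres as "including industrial zones, regions near landfill sites, and coastal areas", but does not say which centre is of which kind or how the kinds fall across the arms. The same section also says that "the control group was recruited from a different health center in a separate subdistrict administrative unit that did not receive moringa supplementation".

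Strengths and Limitations accepts that differences in pollution source or background exposure may confound the results. It does not link this to the location subgroup.

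**The concern.** A subgroup result on effect modification compares the treatment effect across strata, so each stratum must supply a treatment effect of its own. If a stratum holds only one arm, all it can supply is how that arm changed over eight weeks. That change mixes any moringa effect with whatever else moved the biomarkers over the period, and a control stratum contains no moringa effect at all.

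A table of results by area could then be read as moringa working better in some parts of the city when it shows area differences or time trends. The article invites that reading. Study Design presents the use of separate locations as a way to evaluate the supplement in different settings, and Participant Recruitment suggests that the variety of sites may help the findings generalise across kinds of urban pollution. The caution offered, limited power, implies that a larger study of the same layout would settle the matter. For centre or subdistrict it would not.

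**Working it through.** The plan gives no figure for this analysis, so there is none to reproduce. The check is structural.

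**Inputs.** Six centres, three wholly intervention and three wholly control (Participant Recruitment). At least three kinds of setting are named: industrial, landfill, coastal. The effect measure is the difference in change between arms (Data Analysis).

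**Step 1: location taken as centre or subdistrict.** Let the mean change in centre c be δ_c + τ_c·A_c. Here δ_c is the change that would occur without moringa, τ_c is the moringa effect in that centre, and A_c is 1 for intervention and 0 for control.
- An intervention centre shows only the sum δ_c + τ_c. A control centre shows only δ_c.
- Strata holding both arms: 0 of 6.
- Six centre terms plus one arm term make 7 columns, with rank 6.
- Six centre terms plus six arm-by-centre terms make 12 columns, with rank 6. Three of the interaction columns are zero and the other three repeat centre columns.

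No τ_c can be estimated, however many women each centre contributes.

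**Step 2: location taken as pollution source.** Suppose each centre has one type and there are three types. For all three types to hold both arms, each needs at least one of the three intervention centres and at least one of the three control centres. That forces exactly one centre per arm in every type. If a type has two centres from one arm, some other type has none from that arm.

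As an illustration under these assumptions, the ways to assign six centres to three non-empty types number 3^6 − 3·2^6 + 3 = 540:

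| Types holding both arms | Assignments |
|---|---|
| 3 | 3!·3! = 36 |
| 2 | 216 |
| 1 | 252 |
| 0 | 36 |

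So 540 − 36 = 504 assignments leave at least one type with a single arm. Strata of 2 v 1, 3 v 1 or 2 v 2 centres do occur; 54 assignments contain a 2 v 2 stratum. These are counts of possibilities, not probabilities, since the centres were not allocated at random.

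**Step 3: a type with one centre per arm.** The difference-in-differences estimates τ + (δ_I − δ_C), where I and C are the two centres. The bracket is the difference between two centres over time, and nothing in the data separates it from τ.

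To give this a size, assume an intraclass correlation ρ for the change score of 0.01 to 0.05; the article gives none. With m women per centre and unit variance, the variance of the contrast is 2[ρ + (1 − ρ)/m], while an analysis that ignores centre uses 2/m. Assume also that women are spread evenly over three centres per arm.
- 26 per arm, m = 26/3 = 8.67: standard error 0.498 to 0.565, against 0.480 if centre is ignored. A nominal one-sided 0.05 becomes 0.056 to 0.081.
- 59 per arm, m = 59/3 = 19.67: standard error 0.347 to 0.443, against 0.319. It becomes 0.066 to 0.118.

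The error rate is higher with more women, so the problem is not one of power.

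**The case against.** The strongest reply is that location and pollution source are written as a single item and that the article describes its locations by kind of environment. Read that way, a stratum is a pollution type, and a type can span centres of both arms. This stands. A reader might infer that the whole item has no treatment contrast, or that at best it could compare one centre with one other. The documents do not support that: contrasts of 2 v 1, 3 v 1 or 2 v 2 centres are possible under a centre map that the article does not report. Nor can it be presumed that the types are split by arm, because a condensed article may leave the map to the full protocol.

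A reader might also infer that one-arm before-after tests will be run area by area. Data Analysis plans paired tests for each group, not for each location, and uses difference-in-differences and ANCOVA to compare groups. The documents therefore give no basis for a false-positive rate for such tests.

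The analysis is also optional, labelled exploratory, and absent from the examples of exploratory reporting given under Safety and Tolerability. The limitations section admits environmental confounding in general. All of this lowers the weight of the point. It does not answer the part about centre and subdistrict: the stated caution concerns power, and nowhere does the article say that a location stratum may have no comparator.

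**Conclusion.** The point holds in limited form. By centre or subdistrict, none of the six strata contains both arms, so the effect of moringa within a location is not identified. This follows from the design alone and needs no assumption about effect size or variance. By pollution source, a contrast exists only for types with centres in both arms. The article does not show which types these are, and any contrast would rest on very few centres. With one centre per arm, treatment and centre are completely confounded.

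The statement that three types can all have both arms only as 1 v 1 assumes exactly three types and one type per centre; merging types would change it. The error rates of 0.056 to 0.118 illustrate assumed intraclass correlations and are not estimates for this trial. If the singular wording about the control group's health centre were literal, at most one type could have a control, but that wording conflicts with the three control sites stated in the same section.

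Severity is minor: no primary or secondary conclusion depends on this analysis.

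**What to change.** In Data Analysis:
- Remove geographic location, in the sense of centre or subdistrict, from the list of possible effect modifiers.
- Keep pollution source only for types with at least one intervention and one control centre. State which centre falls in which type and arm.
- Report those types as descriptive difference-in-differences estimates with intervals. Say that treatment and centre are confounded and that intervals based on variation between women do not include variation between centres.
- State that before-after changes in areas with one arm will not be presented as moringa effects.
- Give lack of a comparator, not only limited power, as the reason for caution.

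The number of control centres should be stated consistently within Participant Recruitment, since it decides which types can be kept.

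The cost is a change of wording, with no new data. At most, one optional exploratory table is shortened or dropped.
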